### 3.3. Sampling and Sample Size

The sampling process will be conducted using an intentional or convenience sampling approach, wherein all pregnant women who meet the inclusion criteria and are under the care of the project’s principal investigator will be included until the predetermined sample size is reached. This meticulous approach aims to encompass a diverse range of participants, thereby enhancing the generalizability of the study findings.

The calculation was based on the results obtained in a pilot study (unpublished data) with 17 and 23 women in the intervention and control groups, respectively, using the Gpower 3.1.9.4 software. Different calculations were carried out based on the means and standard deviations obtained in the times of the active, passive, and expulsive phases, as well as on the VAS scale (Likert 1–10 points) used to measure pain. From the different calculations carried out, the one that determined the largest sample size (difference of means in time of expulsive phase) was selected with the intention of having sufficient statistical power for all the analyses proposed.

The means and standard deviation obtained for the expulsive phase time (second stage of parturition, which starts at full dilation and continues until birth) in a pilot study were 46 ± 39 min for the intervention group and 65 ± 47 min for the control group. The number of women per group was calculated to determine a difference in the means of independent groups with alpha = 0.05 (type I error), power (1-beta) = 0.8, and allocation n1/n2 ratio = 1, obtaining a total of 166 women (83 in each group) [23].

Recruitment. The selection of participants for this study will adhere to specific criteria outlined as follows:

Inclusion criteria: The study will include pregnant women who meet the following requirements: Women with induced, accelerated, or spontaneous labor, both primiparous and multiparous, are included.Women who are 18 years of age or older and in the term of their pregnancy (37–42 weeks).Single gestation (not multiple pregnancies).Absence of associated pathologies or medical conditions.Proficient communication skills in the Spanish language.

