Exclusion criteria: The study will exclude pregnant women who meet any of the following criteria: Women with a fetus in a breech or transverse presentation.Women who have previously undergone caesarean sections.Women with existing skin lesions or wounds.Women with cognitive deficits or impairments.Women who have consumed toxic substances or medications during their pregnancy.Women with diagnoses of placenta previa (previous insertion placenta), fetal pathologies such as Delayed Intrauterine Growth (DIC) or Small for Gestational Age (SGA), or instances of oligo- or polyhydramnios.

These well-defined criteria will ensure that the study focuses on a specific group of pregnant women, enabling researchers to examine the intended effects of the intervention more accurately. 

Allocation. Assignment to the intervention group will be made by simple randomization of the sample. To do this, a random sequence of numbers will be generated using R software (R 4.1.3, March 2022), which is open source and specifically designed for statistical analysis, to assign women to intervention/control groups. For this purpose, the function will be used: sample (1:166, 83, replace = FALSE). The women who are attended in the order of arrival will be included in the intervention group if their order coincides with any of the random numbers generated.

Intervention. Intervention will be implemented by a single researcher and it will be based on pressure on the points detailed below:

It will start by exerting pressure on:-LI4 of the left hand, SP6 of the left leg, GB21 of the left shoulder, and then the same sequence on the right side. This is intended to generate regular and effective contractions and promote the descent of the fetal head.-Yongquan (R1): For pain relief and relaxation of women, exerting constant pressure for 1 min, as many times as necessary to promote pain control.-Hand points: Also for pain relief, autonomously by the woman, whenever she needs it.

The location of the trigger points can be visualized in Appendix A.

Constant pressure will be generated for 3 min, alternating points, and repeating the technique every 4 h, after the scans. Digital pressure will be applied until half of the nail turns white (equivalent to 3 to 5 kg of pressure) [23]. The Hegu point (LI4) will also serve as an analgesic point.

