The purpose behind administering pressure to different points using fingers in the control group is to eliminate any potential placebo effect associated with “manipulation using a therapeutic instrument”. It is important to note that none of the points pressed in either the intervention group or the control group possess an anatomical location that can induce significant physiological changes when pressure is applied, such as pressing the carotid artery. This precautionary measure ensures the safety of the study participants, minimizing any adverse effects resulting from the applied pressure on the women. Thus, the inclusion of these additional control points not only serves to rule out placebo effects, but also guarantees the well-being and welfare of the participants by preventing any unintended consequences arising from the pressure applied during the study.

Outcomes. Variables will be measured in order to assess the efficacy and safety of the intervention:-Effectiveness of the use of acupressure on labor times in minutes (time of cervical dilatation and time of fetal expulsion according to the recommendations of the World Health Organization).-Effectiveness of the use of acupressure on women’s perceived pain by recording values on the VAS scale and the need for pharmacological analgesic methods. A Visual Analogue Scale (VAS) is a pain rating scale that was first used in 1921 by Hayes and Patterson. The pain VAS is a one-dimensional measure of pain intensity that is used to record the progression of patients’ pain or to compare the severity of pain between patients with similar conditions. The patient must rate their perceived pain on a scale of 0 (no pain) to 10 (the most severe pain imaginable) [1,4,13,14,15,17,19,24,25,26].-Impact of the use of acupressure on maternal satisfaction expressed about the childbirth experience (using the validated satisfaction scale Mackey Satisfaction Childbirth Rating Scale—MSCRS) [8].-Impact of the use of acupressure on neonatal outcomes (Apgar test at 1/5/10 min and arterial blood gases at birth).

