Independent variables.-Sociodemographic: Age (years), country of birth, weight (kg), height (cm), marital status (single, domestic partner, married, divorced, widowed), studies (primary, secondary, superior, postgraduate), employment (employed, unemployed), dysmenorrhea: yes/no (verbalization by the woman of having painful menstruations), fear of childbirth (yes/no), reasons for fear of childbirth (verbalization by the woman), hospital (public/private).-Clinics: date of last period (FUR) and probable date of delivery (FPP), gestational age (weeks of gestation), obstetric formula (pregnancies, abortions, childbirth), estimated fetal weight (kg), fetal weight at birth (kg), type of delivery termination (eutocic, instrumented, caesarean section), special circumstances associated with childbirth (maternal fever, meconium, cord prolapse, antepartum hemorrhage, and uterine rupture), factors associated with the newborn (abnormal registration and altered arterial pH, considering normal values—arterial pH at birth: 7.25–7.45, blood oxygen (PaO2): 60–80 mmHg, blood carbon dioxide (PaCO2): 35–45 mmHg, bicarbonate (HCO3-): 24–26 mEq/L, base excess: ±3.0).-Variables that can affect the effectiveness of the intervention: hospital shift the night before (yes/no), start time of application of the technique (0–24 h), level of saturation of the system (number of women in the service attended by the researcher).

Data analysis. The data obtained will be analyzed with IBM SPSS Statistics v23 software; this will allow for the descriptive analysis of qualitative variables through absolute frequencies and percentages, and of quantitative variables through measures of central tendency, dispersion, and position. On the other hand, a statistical inference analysis will be carried out to evaluate the possible differences between the groups; these will be treated as unpaired samples because there are different women who constituted each group.

The statistical association between qualitative variables will be analyzed using Pearson’s chi-square test or Fisher’s exact test (in 2 × 2 tables when in Pearson’s Chi square, the expected frequencies are less than 5 in more than 20% of the cells). Odd ratio will be calculated as size effect measure for this analysis.

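### Labour type at entry and drug stimulation of labour are not among the listed variables, although the trial admits induced, accelerated and spontaneous labours and tests a technique meant to stimulate contractions

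*Protocol article*

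**What the plan says.** All places are in the protocol article.

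- **Population** (3.3, Inclusion criteria): "Women with induced, accelerated, or spontaneous labor, both primiparous and multiparous, are included".
- **Purpose of the technique** (3.3, Intervention), of the main point sequence: "This is intended to generate regular and effective contractions and promote the descent of the fetal head".
- **Outcome** (Section 2 and 3.3, Outcomes): dilation and expulsion times are Objective 1, and the first outcome listed is "Effectiveness of the use of acupressure on labor times in minutes". Of the several sample-size calculations, "the one that determined the largest sample size (difference of means in time of expulsive phase) was selected".
- **Recorded variables** (3.3, Independent variables): the clinical items include the obstetric formula, which captures parity, and "type of delivery termination (eutocic, instrumented, caesarean section), special circumstances associated with childbirth". Those circumstances are five named complications. A separate group holds variables thought to affect how well the intervention works: the previous night's shift, the clock time of the first application and the midwife's workload.
- **Analysis** (3.3, Data analysis): two-group and multi-group tests, their rank-based alternatives and correlations. No adjusted model of labour time is described.

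**The concern.** The technique and drug stimulation share a purpose: effective contractions. The Introduction says that LI4 acts when contractions are irregular, and that pressure on the ankle point may end once they are regular and effective. On the protocol's own reasoning, then, the effect may depend on whether labour is already being stimulated, and a later need for stimulation is a natural sign of success or failure.

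Pain has such a companion measure, because the need for drug analgesia is an outcome beside the pain score. Labour time has none. If stimulation after allocation were used unequally, a small or a large difference in labour time could partly reflect that use, and the listed data would not show it. What is at stake is the interpretation of the result on which the trial is sized.

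**Working it through.** **1. Labour time does drive the design.** The inputs in Section 3.3 are "46 ± 39 min for the intervention group and 65 ± 47 min for the control group" and "alpha = 0.05 (type I error), power (1-beta) = 0.8, and allocation n1/n2 ratio = 1".

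- Difference: 65 − 46 = 19 min.
- Common SD: √((39² + 47²)/2) = √((1521 + 2209)/2) = √1865 = 43.19 min.
- Standardised difference: 19/43.19 = 0.44.
- A two-sided t test needs 82.07 per arm, rounded up to 83, so 166 in total. This matches the plan. A one-sided test would need 64.57, rounded up to 65, and does not match.

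The protocol names no primary outcome. That labour time is the leading effect measure is inferred from Objective 1, the order of outcomes and this calculation.

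**2. What the lists contain.**

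| Item | Independent variables | Outcomes |
|---|---|---|
| Parity | yes, through the obstetric formula | no |
| How labour ended | yes | no |
| How labour began (spontaneous, induced) | no | no |
| Acceleration, oxytocin or other stimulation | no | no |
| Drug analgesia | no | yes |

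Parity and labour type stand in the same inclusion sentence; only parity is carried into the recorded variables.

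**3. Before and after allocation are different problems.**

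- *Before.* Labour type at entry cannot be caused by the arm. Randomisation balances it in expectation, and chance imbalance is part of the sampling variation that the test already allows for. Without the item, the trial loses precision, a check of imbalance and a description by labour type.
- *After.* Randomisation does not make later stimulation equal. It may change because the technique works, or because someone who knows the arm treats the arms differently. Section 3.2 states that the principal investigator gives both techniques and so cannot be blinded. Section 3.3 places the women under that person's care. Masking the analyst does not address this.

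**4. Chance imbalance at entry.** The allocation code draws 83 of 166 order numbers without replacement and without stratifying. If K of 166 women are induced or accelerated, the number X in the intervention arm is hypergeometric, and the difference in shares is (2X − K)/83. Its SD is (2/83)·√(83·(K/166)·(1 − K/166)·83/165). For K = 83 this is (2/83)·√10.44 = 0.078. The documents do not give K, so the shares below are assumed.

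| Assumed share (K) | SD, points | P(difference ≥ 10 points) | P(difference ≥ 15 points) |
|---|---|---|---|
| 20% (33) | 6.2 | 0.12 | 0.02 |
| 30% (50) | 7.1 | 0.13 | 0.03 |
| 40% (66) | 7.6 | 0.15 | 0.04 |
| 50% (83) | 7.8 | 0.21 | 0.06 |

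A difference of 10 points is not rare; one of 15 points is.

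**5. Post-allocation stimulation.** The documents give no rate of use, no difference by arm and no effect on duration. No figure can be derived for it.

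**The case against.** The strongest reply has four parts.

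- *The article is condensed.* The data-collection notebooks are not shown, and labour type should be known at entry because the inclusion criteria name it. This stands in part: the items may be in the charts, so the sound statement is that they are not among the listed variables. It does not remove the point, because the article gives the list in detail, down to workload and the reference range for carbon dioxide, with a group for variables bearing on effectiveness.
- *Randomisation makes the comparison valid.* This stands. Labour time under usual care, including any later stimulation, is a legitimate randomised comparison.
- *Unequal stimulation is conjecture.* Also fair: no section says who decides on stimulation or how often it is used. That is a reason to record it, not evidence that it will differ.
- *Extra data items alone adjust nothing.* This stands, so the fix must name a model. Its absence from a condensed article is not itself the fault.

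A reader might also infer that the distortion could be as large as the planned 19 min. The documents do not support this. The 19 min is a difference in expulsive-phase time. Labour type at entry would be expected to act largely on dilation time, for which the article gives neither a difference nor an SD. An average saving of an hour or more from stimulation could not come out of a phase averaging 46 to 65 min.

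**Conclusion.** The point holds as a gap in the data to be collected. The trial mixes three labour types, tests a technique meant to stimulate contractions and is sized on labour time, yet lists neither labour type at entry nor stimulation. For labour type the loss is precision and a check of chance imbalance. If 20% to 50% of women are induced or accelerated, an imbalance of 10 points or more has probability 0.12 to 0.21, assuming all 166 places are filled. For stimulation after allocation the loss is interpretive: from the listed data, a labour-time result could not be read in the light of unequal use. The size of any such distortion is unknown. It would go too far to call the comparison biased or to say that the question can never be examined. The gap is worth closing because closing it is cheap.

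**What to change.** 1. In 3.3, Independent variables, add labour type at entry (spontaneous, induced, accelerated) and whether stimulation was already running at the first application. Note its start time, since it is a true baseline item only if it began before allocation.
2. In 3.3, Data analysis, add a linear model of labour time, on a transformed scale if skewed, adjusted for these items and for parity, which is already recorded.
3. In 3.3, Outcomes, add: oxytocin or other stimulation started after the first application (yes/no, time). Compare it by arm and state that labour time is read beside it. Do not adjust labour time for it, because it may be a consequence of the intervention.

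The cost is a few items from the labour chart, one added model and one added comparison, with no change to care or eligibility. Section 4 reports 40 participants so far; their items would have to be taken from the charts in retrospect.

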Based on the research carried out by Dávila Payano and Lazo del Carpio (2016), as for the main researcher, it is essential to maintain a deep and relaxed breath, and to apply deep and lasting pressure, bearing all the weight on the pressure point during the exhalation. Your position will be static, standing, with legs slightly apart, exerting force with your body weight. The manipulation must be constant, energetic, uniform, and delicate, using fingers or knuckles [21].

Control. The control group will receive the application of the technique on points not identified by acupuncture as key points (placebo), but with the same characteristics described above (time, frequency, pressure). Different points will be used as placebo points and will be determined using some of the potentially therapeutic points as references; some of these points will be one F-Cun away from the original points with therapeutic effect. The Cun measurement, derived from acupuncture anatomy, represents the width of the thumb at the joint level and serves as an important anatomical unit in traditional acupuncture practices. In traditional Chinese medicine and acupuncture, the concept of Cun plays a vital role in determining precise anatomical locations for treatment. It is a unit of measurement utilized to establish the distances between acupuncture points on the human body. The Cun measurement is unique to each individual and is derived from the width of the thumb at the joint level. By using the Cun measurement as a standardized reference, acupuncturists can accurately locate specific points for therapeutic intervention. In this study, the F-Cun distance will be employed as a reference point for the placement of placebo points, ensuring consistency and precision in the experimental design [23]. The control points placed an F-Cun away from real acupoints will be GB21 (on the shoulder) and another one will be placed between the knuckles of the index and middle fingers. Additionally, the last one will be 2 F-Cun higher than the SP6 placement (see exact placement in pictures at the end of this paper).

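### The control is said to rule out placebo effects, but the listed sham sites include none for R1 and no self-applied technique, so the claim is unsupported for pain, analgesic use and satisfaction

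*Protocol article*

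**What the plan says.** All references are to section 3.3 of the protocol article unless stated otherwise.

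- **Intervention, scheduled part.** The operator presses LI4, SP6 and GB21, left side then right, for 3 min every 4 h at a force given as 3 to 5 kg. LI4 is also described as an analgesic point.
- **Intervention, on-demand part.** R1 is used as follows: "For pain relief and relaxation of women, exerting constant pressure for 1 min, as many times as necessary to promote pain control". The hand points are described as "Also for pain relief, autonomously by the woman, whenever she needs it".
- **Control, sites.** The sham points are "determined using some of the potentially therapeutic points as references". One is an F-Cun from GB21 on the shoulder, "another one will be placed between the knuckles of the index and middle fingers", and "the last one will be 2 F-Cun higher than the SP6 placement (see exact placement in pictures at the end of this paper").
- **Control, dose.** The technique is given at these sites "but with the same characteristics described above (time, frequency, pressure").
- **Purpose of the control.** The paragraph before Outcomes begins with the aim to "eliminate any potential placebo effect associated with" handling with an instrument. It ends by saying that "the inclusion of these additional control points not only serves to rule out placebo effects".
- **Outcomes.** These include VAS pain, need for pharmacological analgesia, and satisfaction on the MSCRS.

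**The concern.** A sham supports a claim about placebo only for the parts of the treatment that it imitates. Here the two on-demand components, both given for pain relief, appear in the description of one arm only. Operator attention on request and a technique under the woman's own control can each change reported pain, the request for analgesia and satisfaction, whichever point is pressed. Section 3.2 says that one investigator delivers both arms and cannot be blinded, so operator blinding does not offset a difference in attention.

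At stake is how a difference on objectives 2 and 3 is interpreted. If the article's statement is taken at face value, a benefit in pain or satisfaction would be read as free of placebo effects when the described control does not allow that reading.

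**Working it through.** No figure in the plan bears on this point, and the sample size of 166 does not enter it. The check compares the two lists of points.

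**Step 1: components against sham sites.** The active components come from the Intervention paragraph, the control sites from the Control paragraph, and the location of R1 (sole of the foot) from the Introduction. The article does not say which active point the knuckle site stands for, so both readings are shown.

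| Active component | Delivery | Stated pain purpose | Sham site if knuckle = LI4 | Sham site if knuckle = hand points |
|---|---|---|---|---|
| GB21 | operator, scheduled | no | shoulder | shoulder |
| SP6 | operator, scheduled | no | above SP6 | above SP6 |
| LI4 | operator, scheduled | yes | knuckle | none |
| R1 | operator, on demand | yes | none | none |
| Hand points | self-applied, on demand | yes | none | knuckle |

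There are 5 components and 3 sham sites, so 5 − 3 = 2 of 5 have no sham site on either reading. Of the 3 components with a stated pain purpose, 1 has a sham site on either reading. R1 has none on both. The knuckle site is most naturally the LI4 counterpart. Even if it stands for the hand points, it is not described as self-applied.

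**Step 2: what the equality statement covers.** Two readings are possible.

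- *Narrow:* time, frequency and pressure are the three scheduled figures (3 min, every 4 h, 3 to 5 kg). On-demand contact then belongs to the active arm only.
- *Broad:* what stands above also includes R1's own time (1 min) and frequency (as needed). Controls could then receive equal operator contact on request. There would still be no sham site for R1 and no self-applied technique for controls.

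**Step 3: the placebo claim under each reading.** On the narrow reading, both operator contact on request and self-control are unmatched. On the broad reading, contact may be matched but R1 has no sham and self-control remains unmatched. Neither reading supports ruling out placebo effects for the three outcomes named.

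**Step 4: the narrower aim.** The Introduction describes the hand points as pressed with a small comb. The Intervention paragraph does not say whether the trial uses one. If it does, even the aim of removing the effect of an instrument is not met for that component.

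**Step 5: size.** The number of R1 requests is not given. Nor is the total time the midwife spends with each woman, which includes ordinary labour care in both arms. A percentage for excess contact would rest on assumed request rates and on pressing time alone, so none is quoted.

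**The case against.** The strongest reply has four parts.

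- **The equality statement may already cover on-demand use.** This stands as far as operator contact goes. A reader might infer that controls certainly get less contact, or that equality can hold only for the scheduled sessions. The text does not settle either. It does not supply the missing R1 site or a self-applied technique.
- **The placement pictures and Appendix A are not shown, and an article condenses.** This is fair, and the point therefore rests on the text. But the text introduces its third site as the last one, which closes the list. The fault is an affirmative claim that goes further than the list supports, rather than a missing detail.
- **The core contrast is matched.** The Abstract describes the intervention as three points, and the three sham sites fit them if the knuckle site stands for LI4. This holds for the scheduled part. The Intervention paragraph nevertheless adds R1 and the hand points.
- **The placebo sentence should be read within its paragraph, which concerns an instrument.** The context does narrow the aim, but the closing sentence carries no such limit.

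A reader might also go further and conclude that the trial cannot test its hypotheses, or that labour times and neonatal results are compromised. The documents do not support that. Section 2 compares intervention with control as groups, and that comparison remains valid for the package as delivered.

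**Conclusion.** The point holds, and the text should be corrected. As described, the sham has no site for R1 and no self-applied technique, so the statement that placebo effects are ruled out is unsupported for VAS pain, analgesic use and satisfaction. This conclusion does not depend on how the equality statement or the knuckle site is read. It assumes that the pictures not shown add no fourth control site and that the Intervention paragraph, not the Abstract, defines the active treatment.

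The size is structural: 2 of 5 components lack a sham site, and 1 of 3 pain-purpose components has one. The direction and amount of any bias cannot be derived from the article. What is lost is the stronger interpretation of the three outcomes, not the test of group difference.

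**What to change.** 1. In the Control paragraph, state what controls receive on request. If they receive nothing, limit the equality statement to the scheduled points.
2. In the paragraph on the purpose of the control, limit the placebo claim to scheduled finger pressure.
3. Report pain, analgesia and satisfaction as the acupressure package versus a three-point sham.
4. Record by arm the number of operator-applied R1 applications and any on-demand control applications. Record hand-point use as yes/no, since a reliable count of self-applied use in labour is unrealistic.

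The cost is some wording, one extra item on the record form and a weaker placebo claim. No woman's treatment changes.

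Sham R1 and sham hand points under the same on-demand rules are optional, and worth adding only if a placebo-controlled claim for the pain components is wanted. That would need an amendment, operator time, a change of regimen part-way, and analyses with and without the women treated before the change. Section 4 already reports 40 women (17 active, 23 control). Whether they count toward the 166 is unclear, because the sample-size paragraph describes a pilot with the same group sizes.
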